### Secondary outcomes

2.9

The secondary outcomes include the following items: (1) The treatment response rate, which is the proportion of participants with ≥3 mean weekly CSBMs during another assessment period. It will be evaluated at weeks 4, 12 and 20. (2) The percentage of patients with ≥1 increase in mean weekly CSBMs from baseline. It will be evaluated at weeks 4, 8, 12 and 20. (3) The mean weekly CSBMs change from the baseline. It will be evaluated at weeks 4, 8, 12 and 20. (4) Patient Assessment of Constipation-Symptoms (PAC-SYM): a scale to assess the condition of the patient’s constipation-related symptoms. It will be evaluated at weeks 0 and 8. (5) Bristol Stool Scale: a scale to classify the patient’s voluntary bowel movement stool. It will be evaluated at week 0 and 8. (6) Patient Assessment of Constipation Quality of Life Questionnaire (PAC-QOL): a brief but comprehensive assessment of the daily life quality of patients with FC, containing 28 items. It will be evaluated at weeks 0 and 8. (7) Self-rating Anxiety Scale (SAS) (36): a measure of somatic symptoms associated with anxiety reactions. It will be evaluated at weeks 0 and 8. (8) Self-rating Depression Scale (SDS) (37): a self-rating scale to assess patients’ depression. It will be evaluated at weeks 0 and 8. (9) Weekly usage of emergency bowel medications: the proportions of participants using medications and doses for emergency treatment. It will be evaluated from week 1 to week 20.

### Biological specimen exploratory outcomes

2.10

The biological Specimen Analysis Outcomes include the following items: (1) Fecal microbiological outcomes: We will quantify changes in the number and composition of operational taxonomic units (OTUs) of the intestinal microbiota. Changes in intestinal microbiota will be analyzed using 16S rRNA high-throughput detection and the alpha-diversity and beta-diversity will be calculated. Also, high-performance liquid chromatography-mass spectrometry (HPLC-MS) will be used to quantify the amount of intestinal microbiota metabolites Short-chain fatty acids (SCFAs) in fecal. (2) Inflammatory cytokines outcomes: We will use ELISA for serum concentrations of the inflammatory cytokines interleukin-6 (IL-6), interleukin-8 (IL-8), interleukin-10 (IL-10), and tumor necrosis factor-alpha (TNF-α). Fecal and blood samples of the subjects will be collected at week 0 and week 8.

### Safety evaluation

2.11

Adverse events (AEs) of acupuncture include needle sickness, subcutaneous hematoma, localized infection, dizziness, local pain, aggravation of symptoms and other reactions (38). If any AEs occur, the acupuncturist will promptly assess their severity and take appropriate action. Any AEs occurring during the trial should be filled in the “Adverse Event Form” and further investigated. In the event of any serious AEs, they will be reported to the Safety Committee promptly and dealt with proactively. Meanwhile, a final decision will be made on whether to continue the study. In addition, these AEs data will be evaluated by the investigators in terms of severity and causality to determine whether the AEs are associated with acupuncture or sham acupuncture. The incidence of AEs is expressed as the number of AEs (%) during the study.

### Sample size calculation

2.12

The sample size is estimated based on the treatment response rate (the proportion of participants with ≥3 mean weekly CSBMs over weeks 3–8). According to the results of our pre-test, the treatment response rate in the treatment group at week 8 was 31.25% (5/16); The treatment response rate of the control group at week 8 was 6.25% (1/16). The test level was set at α = 0.05 (bilateral), and the test efficacy 1-β = 0.80. According to the calculation made by PASS 15.0, the sample size of each group was 39 cases. Considering the 20% shedding rate, 49 cases will be finally taken from each group, and a total of 98 cases will need to be enrolled in this study.

### Statistical methods

2.13

Statistical analysis will use SPSS 26.0 according to an intention-to-treat analysis. The missing data of the primary outcome will be filled in with the last observation data, while the missing data of safety evaluation will not be filled in. Continuous variables will be expressed as mean ± standard deviation (SD) or median and interquartile range (IQR). The categorical variables will be presented as frequencies or percentages. The *p* value is obtained according to the statistics, and the difference is statistically significant when *p* < 0.05.

Categorical variables, including the treatment response rate (week 8) and the incidence of AEs, will be analyzed using Chi-Square or Fisher’s exact tests. Generalized Estimating Equations (GEE) will be used to compare the data measured repeatedly, including the treatment response rate (week 4, 12, 20), the percentage of patients with ≥1 increase in mean weekly CSBMs from baseline, the mean weekly CSBMs change and Weekly usage of emergency bowel medications. Unpaired *t*-test or Mann–Whitney U test will be used to compare continuous variables between groups, including the mean changes of PAC-SYM, Bristol Stool Scale, PAC-QOL, SAS, and SDS scale.

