#### Sham acupuncture group

2.7.2

Participants in the control group will receive sham acupuncture treatment. Sham points, which are 1 cun lateral to Zhao Hai(KI 6), Da Zhong(KI 4), Tai Xi(KI 3), Tian Shu(ST 25), and Shang Ju Xu(ST 37), will be used to match real acupuncture points. The placebo needles chosen for this study are flat-tipped needles without a tip, which could not be pierced into the skin. In the meanwhile, an external patch device will fix the needles, which are visually pierced into the skin. When the blunt tip of the needle touches the skin, patients will feel a pricking sensation, but without the feeling of de qi. After the treatment, the acupuncturist will press the acupuncture point with a dry cotton ball so that the patient can feel the pulling out of the “needle.” It is worth pointing out that the sham acupuncture device used in this study has been granted a utility model patent by China National Intellectual Property Administration (the Patent Number: ZL 2023 20605629.3).

Participants in both groups will be provided with health education, attention to the dietary regimen, avoidance of irritating foods, and attention to emotional self-regulation. Participants will be asked to keep a stool diary in the study, which is recorded during the baseline period (weeks −1 and 0), the treatment period (weeks 3–8), and the follow-up period (weeks 11, 12, 19, and 20). Moreover, the researcher will instruct patients on how to complete the stool diary. All participants will receive 24 sessions of acupuncture or sham acupuncture three times a week for 8 weeks. All treatments will be performed after skin disinfection, and each treatment will last for 30 min. Meanwhile, every patient will be required to stay in the supine position and wear an eye mask during the treatment.

If the patient has had no bowel movement for 3 or more consecutive days, or if the patient has had serious physical discomfort due to the inability to defecate, he/she can take emergency treatment. To be specific, he/she is allowed to use 20 mL of Glycerine Enema (Glycerine Enema, H31021363, Shanghai Yunjia Huangpu Pharmaceutical Co., Ltd.; 20 mL/bottle). However, the patient is required to strictly record the dose and frequency of medication. At the same time, the investigators will record the patient’s medication in detail on the CRF.

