### Primary outcomes

2.8

The primary outcome of the study is the treatment response rate, which is the proportion of participants with ≥3 mean weekly CSBMs over weeks 3–8. The CSBMs refers to the frequency of a bowel movement that occurs in the absence of laxatives or manipulation. In this study, the mean CSBMs at baseline is calculated by dividing the total number of CSBMs between weeks −1 and 0 by the number of weeks 2. Meanwhile, the mean CSBMs at week 8 is calculated by dividing the total number of CSBMs between weeks 3 and 8 by the number of weeks 6.

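### Last observation carried forward is a poor and underspecified rule for a primary endpoint that classifies participants on a six-week mean

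*Protocol article*

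**What the plan says.** All places are in the protocol article.

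- **2.8 Primary outcomes.** The endpoint is "the proportion of participants with ≥3 mean weekly CSBMs over weeks 3–8". The week-8 mean is obtained by "dividing the total number of CSBMs between weeks 3 and 8 by the number of weeks 6". A responder therefore needs at least 18 CSBMs in six weeks.
- **2.13 Statistical methods.** "Statistical analysis will use SPSS 26.0 according to an intention-to-treat analysis". For gaps: "The missing data of the primary outcome will be filled in with the last observation data". No other handling of missing primary data is given. The primary comparison uses a chi-square or Fisher's exact test.
- **2.7.2 (text common to both groups).** The stool diary covers weeks −1 and 0, weeks 3–8, and four follow-up weeks. None is kept in weeks 1–2.
- **2.9 Secondary outcomes.** The same kind of response rate is also assessed at other visits: "It will be evaluated at weeks 4, 12 and 20".
- **2.12 Sample size calculation.** The pilot rates are 31.25% and 6.25%, giving 39 per group. Then: "Considering the 20% shedding rate, 49 cases will be finally taken from each group".

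**The concern.** Carrying the last observation forward suits an endpoint measured at a single visit better than one that averages six weeks and then applies a cut-off. With weekly counts, the last recorded week stands in for every later one and gets most of the weight in the mean. A single week is far noisier than six, so it pushes participants across the threshold in both directions. Someone who stops treatment also keeps the on-treatment value.

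The rule is incomplete as well. The value carried could be the last weekly count, the week-4 result (a shorter period) or, for someone lost in weeks 1–2, the baseline mean. These can classify the same person differently. Section 2.8 fixes the divisor at 6 without saying how a partly completed diary enters it.

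The stake is the primary test. The expected number of sham responders is small, so a handful of imputed outcomes is not negligible.

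**Working it through.** **1. The plan's own figure.** With p₁ = 5/16, p₂ = 1/16, two-sided α = 0.05, 80% power and pooled variance:

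n = [1.960·√(2·0.1875·0.8125) + 0.842·√(0.2148 + 0.0586)]² / 0.25² = (1.082 + 0.440)² / 0.0625 ≈ 37.1, so 38 per group. The article's 39 is within one of this. Inflation: 39/0.8 = 48.75, so 49. The sample size reproduces.

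**2. How many could be affected.** 0.20 × 49 = 9.8 lost per arm. Expected responders are 49 × 0.3125 = 15.3 and 49 × 0.0625 = 3.1. The 9.8 is an upper figure: 2.12 does not tie the loss to week 8, and losses in weeks 9–20 leave the primary outcome complete.

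**3. What the rule does to one diary (weekly reading).**
- 3 CSBMs in week 3, then nothing: filled, 18/6 = 3.0 (responder). Recorded total over 6, 3/6 = 0.5 (non-responder).
- 4 CSBMs in each of weeks 3–5, then nothing: filled, 24/6 = 4.0 (responder). Recorded total over 6, 12/6 = 2.0 (non-responder).

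**4. Misclassification.** Assume independent weekly Poisson counts with mean m. Full data: P(Poisson(6m) ≥ 18). After k recorded weeks, the filled total is the sum of those k weeks plus (6 − k) times the last one. For k = 1 the condition is simply a count of at least 3. At m = 2 that is 1 − 5e⁻² = 0.323, and at m = 4 it is 1 − 13e⁻⁴ = 0.762.

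| True mean | Full data | k = 1 | k = 2 | k = 3 | k = 4 |
|---|---|---|---|---|---|
| 2 | 6% | 32% | 20% | 18% | 13% |
| 3 | 53% | 58% | 48% | 49% | 51% |
| 4 | 91% | 76% | 72% | 77% | 82% |

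True non-responders are promoted and true responders demoted. Near the threshold little changes on average.

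**5. Effect on the arm difference.** Simulation with Poisson weeks and lognormal patient means (log-SD 0.3, 0.6 or 0.9, an assumption), calibrated to 31.25% and 6.25%. Among patients seen only in week 3, the weekly rule labels 38–45% of acupuncture and 12–24% of sham patients responders.
- If all 20% in both arms left at that point, the arm rates are 0.8 × 31.25% + 0.2 × (38.4 to 45.1%) = 32.7–34.0%, and 0.8 × 6.25% + 0.2 × (12.1 to 24.4%) = 7.4–9.9%. The difference is 24–25 points against 25 planned, with power of 83–89% at 49 per arm.
- Bounds with unequal outcomes among those lost: all acupuncture losses imputed as responders and no sham losses, 45% − 5% = 40 points. The reverse, 25% − 25% = 0 points. These are limits, not forecasts.

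**6. Counting all losses as failures.** The rates become 0.8 × 31.25% = 25% and 0.8 × 6.25% = 5%. Planning formula at 49 per arm: (0.20·√49 − 1.960·√0.255)/√0.235 = 0.846, so power is 80.1%. Exact enumeration gives 84.7% for uncorrected chi-square and 73.5% for Fisher's exact test.

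**The case against.** Several stronger readings are tempting, and the article does not support them.

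- *That 2.13 contradicts 2.8.* It does not. If missing weeks are filled first and six filled weeks are then divided by 6, both rules hold. Section 2.8 nowhere says that unrecorded weeks count as zero. What stands is that the two sections are not reconciled for incomplete diaries.
- *That early drop-outs become responders.* Only those with a high last value do, and only if weekly counts are carried. Participants lost in weeks 1–2 have only baseline to carry, which would normally mean non-response.
- *That the rule favours acupuncture.* Step 5 shows almost no movement when early loss is equal in the two arms.
- *That one reclassified participant decides the trial.* With uncorrected chi-square, 9/49 against 3/49 gives p = 0.064 and 10/49 against 3/49 gives p = 0.037. Under Fisher's exact test, which 2.13 also allows, the values are 0.121 and 0.071 and nothing crosses 0.05. The planning rates imply about 15 against 3 responders, and any missing-data rule can move a borderline result.

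It is also fair to say that multiple imputation and tipping-point analyses are usually left to an analysis plan, so their absence from a condensed article is no fault. That does not rescue the rule itself: the article names it, and names no other for the primary outcome.

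**Conclusion.** The concern holds in this form: the stated rule is unsuited to a six-week-mean responder endpoint, and the article does not say at what level it works. On the weekly reading it misclassifies incomplete diaries in both directions. With one recorded week the responder probability is 32% instead of 6% at a true mean of 2, and 76% instead of 91% at a true mean of 4, assuming independent Poisson weeks. The direction of the net bias is unknown. Equal early loss leaves the difference at 24–25 points, so the exposure lies in loss that differs between arms in timing or reason. Up to about 10 per arm may fall under the rule if the whole 20% is lost before week 8, which the article does not state. The sample size is not in question.

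**What to change.** In 2.13, replace the carry-forward rule. In the primary intention-to-treat analysis, count a participant with fewer than a pre-set number of recorded diary weeks (for example 4 of the 6) as a non-responder. For everyone else use the mean over recorded weeks, and change the divisor in 2.8 from a fixed 6 to the number of recorded weeks. Add multiple imputation of weekly CSBM counts as a sensitivity analysis.

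The minimum number of weeks is the essential part. Averaging recorded weeks without it leaves the one-week problem at 32%. With four recorded weeks and a true mean of 2, averaging gives P(Poisson(8) ≥ 12) = 11% against 13% under carry-forward and 6% with full data, so most of the gain comes from the cut-off.

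The cost is a few sentences and a little analysis work, settled before unblinding. The downside is lower response rates in both arms and some power. If all 20% lost count as failures, power at 49 per arm is about 80% by the planning formula, 85% by uncorrected chi-square and 74% by Fisher's exact test. Because the choice of test matters this much, 2.13 should also name one primary test instead of leaving two open.

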## Abstract

**Introduction:**

Functional constipation (FC) is a common functional gastrointestinal disorder in clinical practice, with the prevalence of which increasing with age. With the increasing aging of the population worldwide, this problem is bound to become more prominent. Acupuncture is effective and recommended for the treatment of FC. However, little is known about how acupuncture affects the gut microbiota and inflammatory cytokines and thus improves gut function. Meanwhile, there are few high-quality clinical trials specifically focusing on acupuncture in treating FC in older people. The objective of this study is to assess the efficacy and safety of acupuncture in treating FC in older people. Additionally, the research aims to explore the mechanism of action of acupuncture in treating FC in older people by affecting intestinal microbiota and inflammation cytokines.

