In recent years, many studies have focused on intestinal flora’s effects on human health, disease, and aging (25–27). It is noteworthy that dysbiosis of the intestinal microbiota is associated with constipation. It is reported that microbial diversity and abundance often decline in patients with constipation (28). In addition, the abundance of beneficial bacteria in the gut decreases with age (29). The gut microbiota of older people is less diverse compared to that of young people (30, 31). Meanwhile, any disturbance in the composition of the microbiota may lead to a reduction in the efficacy of the immune system, which is more pronounced in the elderly. In addition, cytokines play an important role in regulating the immune system’s interactions with the microbiota. As humans age, the function of innate and acquired immune both decreases, and pro-inflammatory mediators, such as acute-phase proteins, cytokines, and adhesion molecules in the bloodstream increase (32).

The selection and combination of acupuncture points, which is a key factor in the clinical effectiveness of acupuncture, is also a characteristic of acupuncture treatment. Meanwhile, we have observed in our clinic that some patients with FC have not only improved their constipation symptoms but also their moods after receiving acupuncture treatment. Consequently, considering this and the efficacy of the combination of acupuncture points and pathological characteristics of FC in older people, we designed this study. We hypothesize that acupuncture might improve clinical symptoms in older patients with FC by modulating intestinal microbial composition and inflammatory cytokines. Consequently, this trial aims to assess the efficacy and safety of acupuncture in treating FC in older people and to explore these mechanisms.

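### The only stated between-group analysis of adverse events is a significance test in a trial sized for response; a confidence interval for the difference would serve the safety objective better

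*Protocol article*

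**What the plan says.** The Abstract puts safety beside efficacy in the objective: "The objective of this study is to assess the efficacy and safety of acupuncture in treating FC in older people". The closing paragraph of the Introduction repeats this: "this trial aims to assess the efficacy and safety of acupuncture in treating FC in older people".

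Section 2.13 (Statistical methods) gives one between-group method for AEs and pairs it with the primary efficacy analysis: "Categorical variables, including the treatment response rate (week 8) and the incidence of AEs, will be analyzed using Chi-Square or Fisher’s exact tests". The general threshold in the same section is that "the difference is statistically significant when *p* < 0.05". Missing safety data are left missing.

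Section 2.12 (Sample size calculation) takes only efficacy into account: "The sample size is estimated based on the treatment response rate". It arrives at 39 per group, raised to 49 per group for 20% loss.

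Section 2.11 (Safety evaluation) adds review of severity and causality by the investigators and referral of serious events to a safety committee. It expresses incidence as a number of events with a percentage. No expected AE incidence, margin or interval for AEs appears in the article.

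**The concern.** A difference test suits efficacy, because there the favourable claim rests on rejecting the null hypothesis. For safety the favourable outcome is failure to reject, and a small sample makes that likely whether or not acupuncture causes more events than sham. If few participants have AEs, the one comparative result that the plan promises will probably be non-significant and will not show how large an excess the trial can rule out.

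The unit of analysis is also loose. A chi-square or Fisher test needs each participant counted once, as having had an AE or not. Section 2.11 describes a count of events, and over 24 sessions one participant can contribute several.

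**Working it through.** **1. The plan's own figure.** Inputs from section 2.12: response 31.25% (5/16) versus 6.25% (1/16), two-sided α = 0.05, power 0.80. With p̄ = (0.3125 + 0.0625)/2 = 0.1875, the pooled-variance formula is

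n = [1.960·√(2p̄(1−p̄)) + 0.842·√(p₁(1−p₁) + p₂(1−p₂))]² / (p₁−p₂)² = 37.1, rounded up to 38 per group.

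The stated 39 is within one patient of this. For 20% loss, 39/0.8 = 48.75, rounded up to 49. The figure stands, and it contains nothing about AEs.

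**2. What 49 per arm can detect for AEs.** The document gives no AE incidence, so every rate below is an assumption: a sham rate s, tripled to 3s under acupuncture. For each pair, all 50 × 50 possible tables were enumerated, and the miss probability is

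1 − Σ Bin(a; 49, 3s) · Bin(b; 49, s), summed over the tables (a, b) with two-sided p < 0.05.

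| Assumed sham vs acupuncture | Missed, uncorrected chi-square | Missed, Fisher |
|---|---|---|
| 2% vs 6% | 84.5% | 97.0% |
| 3% vs 9% | 73.9% | 91.1% |
| 5% vs 15% | 58.5% | 76.5% |
| 8% vs 24% | 38.5% | 52.3% |
| 10% vs 30% | 27.5% | 37.3% |
| 15% vs 45% | 8.4% | 12.1% |

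Section 2.13 allows either test. Choosing Fisher whenever an expected count is below 5 gives misses of 97% at 2% vs 6% and 66% at 5% vs 15%, so it stays inside the same range.

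**3. What an interval would add.** Take an illustrative result of 7/49 versus 3/49 participants with an AE. Fisher's p is 0.32 and the uncorrected chi-square p is 0.18, so both are non-significant. The observed difference is 14.3% − 6.1% = 8.2 percentage points, with a Newcombe 95% interval from −4.5 to +21.2. The test alone would report no significant difference; the interval shows that an excess of up to about 21 points has not been excluded. Even with no events in an arm of 49, the two-sided exact 95% upper limit is 1 − 0.025^(1/49) = 7.3%.

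**The case against.** The strongest reply is that the document contains no error. It says it will assess safety, compares AE incidence with a standard test, and nowhere equates non-significance with safety. Low power for AEs is ordinary in a trial sized on its primary outcome. Confidence intervals and the wording of safety conclusions are commonly left to an analysis plan, which is not shown, and nothing in the article rules them out. The test is also not the whole safety evaluation, given the review and reporting in section 2.11.

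Most of this stands, and it limits the point. Three stronger readings are not supported:

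- A reader might infer that p > 0.05 will be reported as showing acupuncture to be safe. No section says so.
- A reader might take one miss rate, for example the 59–76% at 5% versus 15%, as a property of 49 per arm. It belongs to that assumed pair only. Section 2.11 counts local pain, dizziness, haematoma and other reactions as AEs, so higher incidences, where the test performs much better, are quite possible.
- A reader might repeat the calculation at 39 per arm. That number is the efficacy requirement before the allowance for loss, not a stated AE denominator. Events recorded before withdrawal can still count.

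What survives is that the article does more than leave a detail open. It names the AE comparison and gives it the same form as the efficacy test. An interval in an unseen plan would help, but the stated method would remain.

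**Conclusion.** The point holds as a cheap improvement of low priority. The only stated between-group AE analysis is a test at p < 0.05 in a trial sized for response. At assumed sham rates of 2–5%, tripled under acupuncture, it would miss the excess about 59–97% of the time. At 10% versus 30% it would miss 28–37%, and at 15% versus 45% only 8–12%.

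These figures rest on assumed incidences, 49 analysed per arm and one yes/no outcome per participant. The conclusion is conditional: if AEs turn out to be infrequent, a non-significant test is weak evidence about safety; if they are common, the test is reasonably informative about a tripling. In either case an interval says more.

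**What to change.** In section 2.13, analyse AEs as the proportion of participants with at least one AE. Report that proportion per arm with an exact 95% confidence interval, and the acupuncture-minus-sham difference with a 95% confidence interval (Newcombe, for example). Base the between-group safety statement on that interval, in particular its upper limit, alongside the planned severity and causality review. Add one sentence saying that p > 0.05 will not be taken as evidence of safety. The test may stay as a supplement.

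In section 2.11, align the definition of incidence so that the percentage refers to participants, and give the number of events separately.

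The cost is a few lines of text and one more column in the AE table, with no extra patients or data. The safety statement may read less favourably than a non-significant p-value would.

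### The five week-8 scales are compared on raw change from baseline; ANCOVA on the week-8 score would be more precise from the same data

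*Protocol article*

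**What the plan says.** Section 2.9 has PAC-SYM, Bristol Stool Scale, PAC-QOL, SAS and SDS each assessed at weeks 0 and 8. For these scales section 2.13 names an unpaired t-test or Mann–Whitney U test, which "will be used to compare continuous variables between groups, including the mean changes of PAC-SYM, Bristol Stool Scale, PAC-QOL, SAS, and SDS scale". No covariate is named.

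For the primary outcome, section 2.13 says: "Categorical variables, including the treatment response rate (week 8) and the incidence of AEs, will be analyzed using Chi-Square" or Fisher's exact tests. The primary responder definition is an absolute threshold and does not use the baseline. A baseline CSBM rate is nevertheless available, since section 2.8 says that "the mean CSBMs at baseline is calculated by dividing the total number of CSBMs between weeks −1 and 0" by two weeks.

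The repeated CSBM outcomes and emergency medication use go to GEE, with covariates not stated.

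**The concern.** Each of the five scales has one baseline and one post-treatment value. The usual choices are then to compare final values, to compare changes, or to compare final values adjusted for baseline (ANCOVA). The plan takes the second. Subtracting the baseline assumes that a one-point difference at week 0 carries through to week 8 as a full point. With an imperfect correlation it carries through only in part, so the change score over-corrects.

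This has two consequences. The comparison is noisier than it need be. And if the arms differ by chance at week 0, the arm with the higher score is expected to fall further by regression to the mean, which enters the estimated treatment difference. Section 2.5 mentions no stratification on baseline scores that would limit such differences. These scales carry the trial's symptom, quality-of-life and mood results, so the precision matters even though they are secondary.

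**Working it through.** **The plan's own figure.** Section 2.12 gives: "The test level was set at α = 0.05 (bilateral), and the test efficacy 1-β = 0.80". For the acupuncture arm it says that "the treatment response rate in the treatment group at week 8 was 31.25% (5/16"), and for the sham arm it says: "The treatment response rate of the control group at week 8 was 6.25% (1/16"). The mean rate is (0.3125 + 0.0625)/2 = 0.1875. With the pooled variance in both terms, n = (1.960 + 0.842)² × 2 × 0.1875 × 0.8125 / 0.25² = 38.3, rounded up to 39, which agrees with "the sample size of each group was 39 cases". Then 39/0.8 = 48.75, rounded up to 49, which agrees with "Considering the 20% shedding rate, 49 cases will be finally taken from each group". The sample size reproduces. It rests on an unadjusted comparison of two proportions, so how the scales are analysed does not affect it.

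**Precision for the scales.** The inputs are 49 per arm (section 2.12), equal SDs at the two visits (assumed, scaled to 1) and correlation ρ (assumed 0.3, 0.5 and 0.7). The article gives no SD or correlation.

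- Per-patient variance of the change score: 2(1−ρ).
- Residual variance under ANCOVA: 1−ρ².
- Ratio: (1−ρ²)/[2(1−ρ)] = (1+ρ)/2, below 1 for every ρ below 1.
- Power under ANCOVA for an effect that has 80% power on the change score: Φ(2.802/√ratio − 1.960).

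| ρ | Change | ANCOVA | Ratio | Extra variance of change score | ANCOVA total matching 98 on change | Power where change score has 80% |
|---|---|---|---|---|---|---|
| 0.3 | 1.40 | 0.91 | 0.65 | 54% | 98 × 0.65 ≈ 64 | 93.5% |
| 0.5 | 1.00 | 0.75 | 0.75 | 33% | 98 × 0.75 ≈ 74 | 90% |
| 0.7 | 0.60 | 0.51 | 0.85 | 18% | 98 × 0.85 ≈ 83 | 86% |

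The direction does not depend on equal SDs. With SDs s₀ and s₁, the change-score variance minus the ANCOVA variance is (s₀² + s₁² − 2ρs₀s₁) − s₁²(1−ρ²) = (s₀ − ρs₁)², which is never negative. The formula ignores the one degree of freedom spent on the slope. It applies to the t-test and is only a guide for Mann–Whitney.

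**Chance imbalance.** Let D be the observed week-0 difference between arms. With equal SDs the regression slope is ρ, so the expected change contrast given D is (true effect) + ρD − D, a shift of −(1−ρ)D. At 49 per arm the standard error of D is √(2/49) = 0.202 SD, so a 1.96-SE difference is about 0.40 SD. It would shift the contrast by about 0.28, 0.20 and 0.12 SD in absolute size at ρ = 0.3, 0.5 and 0.7. A difference that large in either direction occurs in about 5% of trials for any one scale.

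**Whether the same argument reaches the primary.** At 31.25% against 6.25%, the exact power of chi-square is 85% at 39 per arm and 92.5% at 49 per arm. In simulation at 49 per arm (latent-normal response), logistic regression with baseline gave about 92–93%, 95% and 98% at ρ = 0.3, 0.5 and 0.7. With both arms at 6.25%, the likelihood-ratio logistic test rejected in about 7–10% of runs, against an exact 5.9% for chi-square. Only about 49 × 0.0625 ≈ 3 sham responders are expected, so part of the apparent power gain comes from a test that rejects too often.

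**The case against.** The strongest defence is that nothing here is invalid. Randomisation keeps the t-test and Mann–Whitney test on change scores valid and unbiased on average. The imbalance argument is conditional on the difference that happens to arise, and a 0.40 SD difference is uncommon. Every size quoted rests on an assumed ρ, and at ρ = 0.7 the cost is only 18%. The outcomes are secondary. All of this stands and limits the point to efficiency. It does not remove the point, because the tests are named in the article rather than left open, and for a t-test the better method wins at any ρ below 1.

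A reader might infer three stronger things, none of which the documents support.

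- That the plan ignores its baselines. It does not: the five scales are analysed as changes, and two CSBM outcomes are defined relative to baseline.
- That an unadjusted primary test is a fault. Chi-square or Fisher is an accepted test and matches the basis of the sample size. A response rate of 25% instead of 31.25% would make power look short (77% by chi-square at 49 per arm), but that is not the rate in section 2.12.
- That the GEE models omit baseline. Their covariates are not stated, and an article may leave them to the analysis plan.

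**Conclusion.** The point holds for the five scales and only there. The named change-score tests are valid but less precise than ANCOVA on the week-8 score. The change score carries 54%, 33% and 18% more variance at ρ = 0.3, 0.5 and 0.7, given equal SDs and approximately linear relations. Any chance baseline difference stays in the contrast as −(1−ρ)D. The weight is minor to moderate: it is an improvement worth making to secondary analyses. It is not evidence of bias on average or of inflated type I error, and the primary result and the sample size of 98 are unaffected. I am confident of the direction; the size depends on correlations that the article does not give.

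**What to change.** In section 2.13, replace the between-group tests on mean changes with an ANCOVA of each week-8 score (PAC-SYM, Bristol Stool Scale, PAC-QOL, SAS, SDS) on arm and the week-0 score, reporting the adjusted difference with a 95% confidence interval. Name rank-based ANCOVA for scores that are clearly non-normal. Mean changes can still be shown descriptively.

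Keep chi-square or Fisher as the primary test. If an analysis of the primary adjusted for baseline CSBM is wanted, prespecify it as supportive only, and do not base it on a likelihood-ratio logistic test with so few sham responders expected.

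The cost is a change of wording made before unblinding. No new data, visits or patients are needed, and SPSS fits the ANCOVA models.
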